## 9.6. Management of Overdoses, Trial treatment error, or Occupational Exposure

### **Overdose**

For purposes of this trial, an overdose of pembrolizumab will be defined as any dose of greater than 200mg. No specific information is available on the treatment of overdose of pembrolizumab. Appropriate supportive treatment should be provided if clinically indicated. In the event of overdose, the patient should be observed closely for signs of toxicity. Appropriate supportive treatment should be provided if clinically indicated.

Overdoses should be reported on an incident report (see section 14.1). Any adverse events resulting from an overdose should be reported as an SAE (see section 13.2.2 for reporting procedures). Overdoses of pembrolizumab that are in excess of 5 x the protocol specified dose (i.e. >1000mg), with or without adverse events resulting from an overdose, should be reported as an AESI (see section 13.4, Adverse event of special interest, for reporting procedures).

### **Trial treatment error**

Any unintentional error in prescribing, dispensing, or administration of a trial treatment while in the control of a healthcare professional or consumer. The error can be identified either by the trial team at site or by the Sponsor upon review.

Trial Treatment errors should be reported on an incident report (see section 14.1). Any adverse events resulting from a medication error should be reported as an SAE (see section 13.2.2 for reporting procedures).

### **Occupational exposure**

Exposure to a trial treatment as a result of one's professional or non-professional occupation. Occupational exposure should be reported on an incident report form (see section 14.1).

## 9.7. Supportive Care

Patients should receive appropriate supportive care measures as deemed necessary by the treating investigator. Suggested supportive care measures for the management of adverse events with potential immunologic aetiology are outlined below. Where appropriate, these guidelines include the use of oral or intravenous treatment with

## PEACOCC

---

corticosteroids as well as additional anti-inflammatory agents if symptoms do not improve with administration of corticosteroids. Note that several courses of steroid tapering may be necessary as symptoms may worsen when the steroid dose is decreased. For each disorder, attempts should be made to rule out other causes such as metastatic disease or bacterial or viral infection, which might require additional supportive care. The management guidelines are intended to be applied when the investigator determines the events to be related to pembrolizumab.

Note: if after the evaluation the event is determined not to be related, the investigator does not need to follow the treatment guidance (as outlined in section 9.5). Refer to Section 9.4 for dose delay.

It may be necessary to perform additional procedures such as bronchoscopy, endoscopy, or skin photography as part of evaluation of the event.

## 9.8. Contraindications

Medications or vaccinations specifically prohibited in the exclusion criteria in section 7.2.2 are not allowed during the ongoing trial. If there is a clinical indication for one of these or other medications or vaccinations specifically prohibited during the trial, discontinuation from trial therapy may be required. The investigator should discuss any questions regarding this with the Sponsor. The final decision on any supportive therapy or vaccination rests with the investigator and/or the patient's primary physician.

### 9.8.1. Acceptable Concomitant Medications

All treatments that the investigator considers necessary for a patient's welfare may be administered at the discretion of the investigator in keeping with the community standards of medical care. All concomitant medication will be recorded on the eCRF including all prescription, over-the-counter (OTC), herbal supplements, and IV medications and fluids. If changes occur during the trial period, documentation of drug dosage, frequency, route, and date may also be included on the eCRF. The latest version of the IB should be checked to avoid giving the patient prohibited concomitant medications.

All concomitant medications received within 28 days before the first dose of trial treatment and 30 days after the last dose of trial treatment should be recorded. Concomitant medications administered after 30 days after the last dose of trial treatment should be recorded for SAEs and AESIs as defined in Section 13.

### COVID-19 Vaccinations:

Even though no interaction studies have been performed, the PEACOCC Trial Management Group approve of the use of COVID-19 vaccines in existing PEACOCC participants in the absence of any other contraindications without treatment interruption, and would not exclude future potential participants if they have received a COVID-19 vaccination.

The timing between COVID-19 vaccine administration and trial IMP (pembrolizumab) should be determined by the Principal Investigator or a Co-investigator at site in the best interests of the patient. However, the PEACOCC TMG recommend that there should be a 24-hour gap between vaccine administration and patients receiving pembrolizumab. If you have any questions or would like advice from the PEACOCC TMG please email the trial team at [[contact]](mailto:[contact]). Details of vaccine administration should be added to the concomitant medication eCRF (if received with the timeframe for reporting concomitant medication) and recorded in the patient's medical notes.

### 9.8.2. Prohibited Concomitant Medications\Therapies

Patients are prohibited from receiving the following therapies during the screening and treatment period (including retreatment for post-complete response relapse) of this trial:

- Antineoplastic systemic chemotherapy, endocrine therapy or biological therapy except for treatment to manage hypercalcaemia of malignancy (for example bisphosphonates, denosumab).
- Immunotherapy not specified in this protocol.
- Chemotherapy not specified in this protocol.
- Investigational agents other than pembrolizumab.

Radiation therapy

Note: Radiation therapy to a symptomatic solitary lesion or to the brain may be allowed at the investigator's discretion. If the radiation is delivered to a RECIST v1.1 target lesion which is already used to assess response within the trial, this must first be discussed with the sponsor.

- Live vaccines within 30 days prior to the first dose of trial treatment and while participating in the trial (which includes follow-up). Examples of live vaccines include, but are not limited to, the following: measles, mumps, rubella, varicella/zoster, yellow fever, rabies, BCG, and typhoid vaccine.
- Systemic glucocorticoids for any purpose other than to modulate symptoms from an event of clinical interest of suspected immunologic etiology. The use of physiologic doses of corticosteroids at daily doses equivalent to or less than 10mg prednisolone is allowed.

Patients who, in the assessment by the investigator, require the use of any of the aforementioned treatments for clinical management should be removed from receiving trial treatment and must let UCL CTC know if this occurs. Patients may receive other medications that the investigator deems to be medically necessary.

The Exclusion Criteria describes other medications which are prohibited in this trial.

## PEACOCC

---

### 9.9. Pharmacy Responsibilities

Oversight of all pharmacy aspects of the trial at participating sites is the responsibility of the PI, who may delegate responsibility of specific pharmacy related tasks to the local pharmacist or other appropriately qualified personnel, who will be the Pharmacy Lead. The delegation of duties must be recorded on the site staff delegation log.

Pembrolizumab supplied for the PEACOCC trial are for PEACOCC trial patients only and must not be used outside the context of this protocol.

#### 9.9.1. Storage and Handling Requirements

Clinical supplies must be stored in a secure, limited-access location under the storage conditions specified on the label. Receipt and dispensing of trial medication must be recorded by an authorised person at the trial site. Clinical trial supplies may not be used for any purpose other than that stated in the protocol.

#### 9.9.2. Temperature Excursions

Pembrolizumab drug product must be stored under refrigerated conditions (2°C to 8°C). All temperature excursions outside the storage conditions specified in the IB, SoDA and label must be reported to UCL CTC as per the 'Pharmacy Procedure for Reporting Temperature Excursions' (see Pharmacy Site File).

Upon identifying an excursion:

- all affected trial stock must be quarantined IMMEDIATELY.
- the 'Notification of Temperature Excursion' form must be completed and e-mailed to [[contact]](mailto:[contact])

**Please note that UCL CTC must be informed immediately if any patient has been administered drug affected by a temperature excursion.**

#### 9.9.3. Study IMP Accountability

The Pharmacy Lead must ensure that appropriate records are maintained.

These records must include accountability for the study IMP including: receipt, dispensing, reconciliation and destruction of unused medication (on sponsor authorisation). Accountability forms will be supplied, and must be used, unless there is prior agreement from UCL CTC to use alternative in-house records.

Copies of completed drug accountability logs must be submitted to UCL CTC for all trial patients upon request. Also refer to section 15.2 (Centralised Monitoring).

#### 9.9.4. Returns and Reconciliation

The investigator and lead pharmacist are responsible for keeping accurate records of the clinical trial supplies received from MSD or designee, the amount dispensed to the patients and the amount remaining in stock prior to the conclusion of the trial.

Upon completion or termination of the study, all unused and/or partially used investigational product will be destroyed at the site per institutional policy. It is the Investigator's responsibility to arrange for disposal of all empty containers, provided that procedures for proper disposal have been established according to applicable federal, state, local and institutional guidelines and procedures, and provided that appropriate records of disposal are kept.

## 9.11. Clinical Management after Treatment Discontinuation

If a patient discontinues trial treatment early, they will remain on trial for follow up purposes unless they explicitly withdraw consent. Also refer to sections 10 (Assessments) and 16 (Withdrawal of Patients) for further details regarding treatment discontinuation, patient withdrawal from trial treatment and withdrawal of consent to data collection.

## 9.12. Drug Provision during the trial

During the trial, study IMP, Pembrolizumab will be provided to patients for a maximum of two years in the initial treatment stage.. Patients who stop pembrolizumab with stable disease or better may be eligible for up to one year of re-treatment as per section 9.3.3.

## 10. ASSESSMENTS/TRIAL PROCEDURES

The Trial Schedule of Procedures/Assessments table (Appendix 1) summarises the trial procedures to be performed prior or at each visit. Individual trial procedures are described in detail below. It may be necessary to perform these procedures at unscheduled time points if deemed clinically necessary by the investigator.

### 10.1. Pre-registration Assessments/Procedures

Please refer to section 8.1.1 Pre-registration Assessments

### 10.2. Assessments During Treatment

During treatment (initial and re-treatment) the patient should be seen every 3 weeks from the start of treatment and the following assessments/investigations/procedures. These assessments need to be performed within 3 days prior to day 1 of each cycle, after cycle 1 (Please also see Appendix 1), unless otherwise indicated below:

- **Full physical exam**
- **Vital signs and weight**
- **ECOG PS**
- **Adverse events** review
- **Concomitant medication** review
- **CT scan of chest, assessable by RECIST v1.1**
- **CT scan or MRI scan** assessable by RECIST v1.1 (abdomen, pelvis, and brain, if patient shown to have brain metastases at baseline) (at week 6, week 12 and then every 12 weeks). If a patient's treatment is delayed, the scans should still be performed at these given timepoints where feasible.
- **Full blood count**
- **Liver function tests, urea & electrolytes**
- **Thyroid function tests** (Total T3/Free T4 and TSH)
- **Serum calcium**
- **Urinalysis**
- **Urine or serum pregnancy test** (if applicable)
- **CA 125**
- **Biopsy** (required at 6-8 weeks following treatment initiation)\*.
- **Exploratory research bloods:** PBMCs and plasma – please refer to the lab manual.
- **QoL: FACT-O** (at week 6, week 12 and then every 12 weeks).

\*In the event of any local covid-19 restrictions impacting resource at site to perform the biopsy as scheduled, the biopsy may be performed at a subsequent cycle, if it becomes possible and safe to do so later on. Site must contact the CTC prior to this been re-arranged for approval from the CI/TMG.

### 10.2.1. Adverse Event (AE) Monitoring

The investigator or qualified designee will assess each patient to evaluate for potential new or worsening AEs and more frequently if clinically indicated. AEs will be graded and recorded throughout the study and during the follow-up period according to NCI CTCAE Version 5. AEs will be characterised in terms regarding seriousness, causality, grading, and action taken with regard to trial treatment.

Please refer to Section 13.2 for detailed information regarding the assessment and recording of AEs.

### 10.2.2. Full Physical Exam

The investigator or qualified designee will perform a complete physical exam at each scheduled trial visit.

### 10.2.3. Vital Signs

The investigator or qualified designee will take vital signs at screening, prior to the administration of each dose of trial treatment and at treatment discontinuation as specified in (Appendix 1). Vital signs should include temperature, heart rate, respiratory rate, weight, blood pressure and O2 saturation. Height will be measured at baseline only.

### 10.2.4. ECOG Performance status

The investigator or qualified designee will assess ECOG status at baseline, prior to the administration of each dose of trial treatment and discontinuation of trial treatment as specified in the schedule of events (Appendix 1).

### 10.2.5. Laboratory Procedures/Assessments

Details regarding specific laboratory procedures/assessments to be performed in this trial are provided below laboratory safety evaluations (Haematology, Chemistry and Urinalysis). Laboratory tests for haematology, chemistry, urinalysis, and others are specified in Table 6.

**Table 6 Laboratory Tests**

| Haematology                  | Chemistry                        | Urinalysis             | Other                                        |
|------------------------------|----------------------------------|------------------------|----------------------------------------------|
|                              | Albumin                          | Blood                  | Serum $\beta$ -human chorionic gonadotropin† |
| Haemoglobin                  | Alkaline phosphatase             | Glucose                | ( $\beta$ -hCG)†                             |
| Platelet count               | Alanine aminotransferase (ALT)   | Protein                | PT (INR)                                     |
| WBC (total and differential) | Aspartate aminotransferase (AST) |                        |                                              |
|                              | Lactate dehydrogenase (LDH)      |                        | Total triiodothyronine (T3)                  |
| Absolute Neutrophil Count    |                                  | results are noted      | Free thyroxine (T4)                          |
|                              |                                  | Urine pregnancy test † | Thyroid stimulating hormone (TSH)            |
|                              |                                  |                        |                                              |
|                              | Calcium                          |                        |                                              |
|                              | Chloride                         |                        | Blood for exploratory research studies       |
|                              | Glucose                          |                        |                                              |
|                              | Phosphorus                       |                        |                                              |
|                              | Potassium                        |                        |                                              |

## PEACOC

| Haematology                                                                                                                                             | Chemistry                                                                                  | Urinalysis | Other |
|---------------------------------------------------------------------------------------------------------------------------------------------------------|--------------------------------------------------------------------------------------------|------------|-------|
|                                                                                                                                                         | Sodium                                                                                     |            |       |
|                                                                                                                                                         | Magnesium                                                                                  |            |       |
|                                                                                                                                                         | Total Bilirubin                                                                            |            |       |
|                                                                                                                                                         | Direct Bilirubin ( If total bilirubin is elevated above the upper limit of normal ) |            |       |
|                                                                                                                                                         | Creatinine                                                                                 |            |       |
| † Perform on women of childbearing potential only. If urine pregnancy results cannot be confirmed as negative, a serum pregnancy test will be required. |                                                                                            |            |       |
| ‡ If considered standard of care in your region.                                                                                                        |                                                                                            |            |       |

Laboratory tests for baseline entry for initial treatment and entry into the re-treatment period should be performed within the 10 days prior to registration. After Cycle 1, pre-dose laboratory procedures can be conducted up to 72 hours prior to dosing. Results must be reviewed by the investigator or qualified designee and found to be acceptable prior to each dose of trial treatment.

### 10.3. Tumour Imaging and assessment of disease

#### 10.3.1. Evaluation of Efficacy

Tumour assessments will be based on RECIST v1.1 and will be performed according to the schedule presented in Appendix 1. Tumour assessments will be performed at baseline, after cycle 2 (6 weeks on treatment) and after cycle 4 (12 weeks on treatment) and thereafter after every 4 cycles (12 weekly) until progression.

#### 10.3.2. Tumour Assessment

Tumour assessments can include either cross-sectional imaging using CT or magnetic resonance imaging (MRI) scan of the chest, abdomen, and pelvis; CT or MRI scan of the brain will be performed at baseline. Post-baseline brain imaging will be performed for all patients with brain metastases at baseline or if the patient becomes neurologically symptomatic. The preferred method of disease assessment is CT with contrast. If CT with contrast is contraindicated, CT without contrast or MRI with contrast may be used. The same method is required for all subsequent tumour assessments.

##### 10.3.2.1. CT scans with contrast to the chest, abdomen, pelvis, and brain

CT scans should be performed with contiguous cuts in slice thickness of 5 mm or less. Spiral CT should be performed using a 5 mm contiguous reconstruction algorithm.

##### 10.3.2.2. MRI Imaging scans

MRI of the chest, abdomen and pelvis, and brain is acceptable for measurement of lesions provided that the same anatomical plane is used for serial assessments. If possible, the same imaging device should be used for serial evaluations. In case of MRI, measurements will be preferably performed in the axial (transverse) plane on contrast-enhanced T1-weighted images. However, there are no specific sequence recommendations.

## 10.4. Other Procedures

### 10.4.1. Withdrawal/ Discontinuation

When a patient discontinues/withdraws prior to trial completion, all applicable activities scheduled for the final trial visit should be performed. Any adverse events should be reported in accordance with the safety requirements outlined in Section 13.2. Patients who a) attain a CR or b) complete 24 months of treatment with pembrolizumab may discontinue treatment with the option of restarting treatment if they meet the criteria specified in Section 9.3.3 and the trial remains open. After discontinuing treatment, patients should return to the site for the end of treatment visit as per section 10.5 and then proceed to the Follow-Up period of the study (as per section 10. 6).

### 10.4.2. Visit Requirements

Please also refer to tables of assessments outlined in Appendix 1 'Schedule of Procedures/Assessments'.

#### 10.4.2.1. Baseline

Section 10.1 shows all procedures to be conducted at the baseline visit. All baseline investigations must be completed within the 28 days prior to registration unless otherwise indicated.

#### 10.4.2.2. Treatment period

Procedures to be conducted during the initial and re-treatment period are presented in Appendix 1 'Schedule of Procedures/Assessments'. At study visits, when patients do not receive investigational product, all of the pre-treatment cycle assessments will be performed. All samples are collected pre-dose unless otherwise indicated.

#### 10.4.2.3 Post-Treatment Visits

Appendix 1 'Schedule of Procedures/Assessments' shows all procedures to be conducted during the follow-up period.

All patients are required to attend the end of treatment visit, all follow-up visits and to be contacted by the research team for survival status in accordance with the Schedule of Procedures/Assessments in Appendix 1. However, if a patient discontinues from treatment, has progressed and moves onto alternative anticancer treatment, the follow-up visits will no longer be required; however, survival follow-up assessments and collection of subsequent anticancer therapy information would be required as indicated in the Schedule of Assessments/Procedures, Appendix 1 unless the patient withdraws consent for further survival follow-up. Survival follow-up will continue until the end of study.

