## 10.6. Assessments During Follow Up (before progression)

Patients will have post-treatment follow-up for disease status, until disease progression, death, withdrawing consent, or becoming lost to follow-up.

These patients who discontinue trial treatment for a reason other than disease progression should be assessed **every 12 weeks** ( $84 \pm 7$  days), following the end of treatment, by radiologic imaging to monitor disease status. Every effort should be made to collect information regarding disease status until disease progression, death, end of the study or if the patient begins re-treatment with pembrolizumab as detailed in Section 9.3.3. Information regarding post-study anti-cancer treatment will be collected if new treatment is initiated.

Patients who are eligible and have consented to receive re-treatment with pembrolizumab according to the criteria in Section 9.3.3 will move from the follow-up phase to the re-treatment period when they experience disease progression.

Assessments to be completed during follow-up are:

- **Adverse Events review** as per requirements detailed in the pharmacovigilance sections 13.2.1 (AE), 13.2.2 (SAE) and 13.4 (AESI)
- **CT scan of chest, assessable by RECIST v1.1**
- **CT scan or MRI scan** assessable by RECIST v1.1) (abdomen, pelvis, and brain (if patient assessed with brain metastases at baseline)
- **Additional anti-cancer treatment review**
- **Survival status**
- **QoL: FACT-O**
- **Biopsy** (if first disease progression on the trial during the follow-up period has been confirmed) – should be performed within 6 weeks\*.

\*In the event of any local covid-19 restrictions impacting resource at site to perform the biopsy as scheduled, the biopsy may be performed at a later timepoint, if it becomes possible and safe to do so later on, and as long as the patient has not proceeded with further cancer treatment Site must contact the CTC prior to this been re-arranged for approval from the CI/TMG.

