### 10.6.1. Survival Follow-up

Once a patient experiences confirmed disease progression or starts a new anti-cancer therapy, the patient moves into the survival follow-up phase and should be contacted by telephone every 12 weeks to assess for survival status and any AEs that require reporting as per section 13.2, until death, withdrawal of consent, or the end of the study, whichever occurs first.

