## **18. STATISTICS**

### **18.1. Sample Size Calculation**

Assuming that the proportion of progression-free patients at 12 weeks will be 33%, a proportion <15% would be of no further interest [16]. Using A'hern's single-stage phase II design with 90% power and one-sided 5% significance level, a sample size of 48 patients is required with  $\geq 12$  patients alive and progression-free at 12 weeks to warrant further investigation. The sample size was calculated using "Sample size tables for clinical studies" software.

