### **18.2. Statistical analysis**

#### **18.2.1. Analysis of main endpoint**

The number and percentage of progression-free patients at 12 weeks will be presented, with 90% two-sided confidence intervals for the percentage.

The proportion of progression-free patients is defined as the number of patients alive with complete or partial response or stable disease maintained at 12 weeks (as assessed by the site radiologist and/or investigator, using RECIST v1.1) divided by the number of patients in the analysis population. Only patients with tumour assessment at or beyond 12 weeks will be considered progression-free.

All eligible patients who received at least one cycle of pembrolizumab will be included in the analysis population (i.e. safety population).

Any patient found to be ineligible will be excluded and replaced.

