### **18.2.2.4. Objective response at 12 weeks and best objective response**

Objective response is defined as a complete or partial response as determined by RECIST v1.1. Patients without a tumour assessment at 12 weeks will be considered to be non-responders. The proportion of patients with objective response at 12 weeks will be presented as a proportion with 90% two-sided confidence interval.

The best objective response consists of the best among all objective responses assessed. Best objective response will be reported as a proportion with 90% two-sided confidence interval. The analysis of best objective response will be performed with all patients over the whole study period (including Re-treatment phase). A subset analysis will be performed for patients in the Re-treatment phase, once over the whole study period and once over the Re-treatment phase only.

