|                           | 
a = Pre-existing conditions prior to start of treatment are added as medical history data, any conditions that worsen after treatment then require reporting as an AE.
 
b = Pregnancy testing required within 3 days prior to registration.
 
c = Pre-cycle 1, day 1 treatment bloods to be performed within 10 days prior to registration i.e. they do not need to be repeated following baseline for day 1 cycle 1.
 
d = Ca125 to be performed within 14 days prior to registration.
 
e = Re-biopsy 6-8 weeks during treatment and upon progression.
 
f = exploratory bloods at cycles 2, 4 & 6, then at 12 months only.
 
g = At the time of disease progression.
 
h = AEs 30 days post last treatment, SAEs up until 110 days post last treatment and longer if a late term SAR, and AESIs up until 110 days post treatment.
 
i = Archival tissue collected.
 
j = If patient has not progressed, imaging, CA125 and QoL continues until progression.
 
K = Baseline exploratory bloods can also be taken after registration and pre cycle 1 day 1, if logistically more suitable to take at that time.
 
L= Imaging & QoL every 12 weeks until end of treatment (also see code J).
 |                                                                 |                                                                                                           |   |   |   |   |   |   |   |   |                                              |                                            |                                     |

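### For a patient who starts another systemic anticancer drug without having progressed, the protocol gives conflicting imaging rules, so the same patient can be a 12-week success or failure.

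*Protocol*

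**What the plan says.** **Imaging after treatment stops.** Protocol 10.4.2.3 requires all patients to attend all follow-up visits, with one exception: "if a patient discontinues from treatment, has progressed and moves onto alternative anticancer treatment, the follow-up visits will no longer be required". Section 10.6 says: "Patients will have post-treatment follow-up for disease status, until disease progression, death, withdrawing consent, or becoming lost to follow-up". It sets imaging every 12 weeks for patients who stop for a reason other than progression, and has new anticancer treatment recorded without making it a reason to stop imaging. Appendix 1 note j says: "If patient has not progressed, imaging, CA125 and QoL continues until progression". Section 10.6.1 says: "Once a patient experiences confirmed disease progression or starts a new anti-cancer therapy, the patient moves into the survival follow-up phase". That phase is a telephone contact every 12 weeks, and the survival follow-up column of Appendix 1 has no imaging.

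**Endpoints.** Section 18.2.1 defines success as being alive with complete response, partial response or stable disease maintained at 12 weeks, and adds: "Only patients with tumour assessment at or beyond 12 weeks will be considered progression-free". The denominator is all eligible patients with at least one cycle, so early discontinuers stay in. Section 18.2.2.4 says: "The best objective response consists of the best among all objective responses assessed". Neither section mentions other anticancer therapy. Section 9.8.2 takes a patient who needs prohibited therapy off trial treatment and states no consequence for the endpoints. Section 9.11 keeps early discontinuers in follow-up.

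**Design.** Section 18.1: "Assuming that the proportion of progression-free patients at 12 weeks will be 33%, a proportion <15% would be of no further interest"; "single-stage phase II design with 90% power and one-sided 5% significance level, a sample size of 48 patients is required", with at least 12 patients progression-free needed.

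**The concern.** Section 9.3.2 allows treatment to stop without progression, for example for toxicity, intercurrent illness, or the investigator's or patient's decision. Suppose this happens before week 12 and the patient starts another systemic drug. Whether a later scan exists depends on which passage the site follows. If it exists and shows no progression, 18.2.1 as written counts the patient as a success.

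In a single-arm trial every such patient is attributed to pembrolizumab, and no control arm absorbs the effect. The threshold is also tight. By exact 90% intervals, 12 of 48 gives 15.1% to 37.3% and 11 of 48 gives 13.4% to 35.1%, so one patient decides whether 15% is excluded.

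**Working it through.** **1. The passages side by side.** Take a patient off pembrolizumab, not progressed, who has started another systemic drug.

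| Protocol section | Condition that ends imaging | This patient | Status under 18.2.1 if later scans would show no progression |
|---|---|---|---|
| 10.4.2.3 | progression AND new therapy | still imaged | success |
| 10.6 | progression (new therapy only recorded) | still imaged | success |
| Appendix 1, note j | progression | still imaged | success |
| 10.6.1 | progression OR new therapy | telephone only | failure (no qualifying scan) |

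On this patient the text divides three to one.

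**2. Can the qualifying scan fall after the switch?** The end-of-treatment visit is 30 ± 7 days after the last dose or the decision to discontinue (10.5). Imaging then follows every 12 weeks (10.6). Counting from the last dose, 30/7 = 4.3 weeks:

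- Last dose week 0: visit at week 4.3, next scan at week 4.3 + 12 = 16.3.
- Last dose week 3: visit at week 7.3, next scan at week 19.3.
- Last dose week 6: visit at week 10.3, next scan at week 22.3.

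The later scan meets the requirement in 18.2.1, which has no upper time limit, and it can be taken on another drug.

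**3. The plan's own design figure.** Inputs from 18.1: n = 48, threshold 12, null 15%, alternative 33%. By the exact binomial:

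- P(X ≥ 12 | n = 48, p = 0.15) = 0.0478
- P(X ≥ 12 | n = 48, p = 0.33) = 0.911

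A search confirms that 48 with threshold 12 is the smallest design meeting one-sided 5% and 90% power, so the stated design reproduces.

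**4. Effect on the false-positive probability.** Let m of the 48 be switchers, each counted as a success with probability q, and let the other 48 − m have a true rate of 15%. Then

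P(positive) = Σ over j = 0..m of C(m, j) q^j (1 − q)^(m − j) × P(X ≥ 12 − j | n = 48 − m, p = 0.15).

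For m = 1 and q = 0.5: 0.5 × P(X ≥ 12 | 47) + 0.5 × P(X ≥ 11 | 47) = 0.5 × 0.0413 + 0.5 × 0.0846 = 0.063.

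The protocol gives neither m nor q, so both are assumptions:

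| q | m = 1 | m = 2 | m = 3 |
|---|---|---|---|
| 8% | 4.5% | 4.2% | 3.9% |
| 15% | 4.8% | 4.8% | 4.8% |
| 33% | 5.6% | 6.4% | 7.4% |
| 50% | 6.3% | 8.2% | 10.4% |
| 100% | 8.5% | 14.2% | 22.5% |

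The last row is the upper bound. Each credited patient adds 1/48 = 2.1 percentage points to the observed primary rate.

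**The case against.** **It belongs in the SAP.** Handling of therapy started after trial treatment is commonly left to the SAP, which is not shown. Counting outcomes regardless of later therapy can also be a deliberate choice: the PFS definition includes all deaths, on study or after treatment stops. This stands in part, and silence alone would be no finding. But the protocol itself fixes the success definition and the imaging schedule, and the schedule contradicts itself. An SAP cannot recover scans that sites following 10.6.1 never took.

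**10.6.1 is the specific rule and should govern.** It is the only passage that says follow-up changes on new therapy without progression, and it gives the conservative result. The protocol does not state that it prevails, and the other three passages point the other way.

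**The route is narrow and the other drug may do little.** The patient must switch before progressing and then be progression-free on a scan usually near weeks 16 to 22, a harder test than week 12. Section 2.1.1 cites second-line chemotherapy response rates as low as 0–8% in ovarian clear cell disease. This stands, and it is why the figures are given as a range.

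**Stronger readings that the documents do not support.**
- A reader might infer that four passages give four answers. They divide three to one, and the exception quoted from 10.4.2.3 covers patients who have already progressed and are failures anyway. The sharpest clash is 10.6.1 against 10.6 and note j.
- A reader might infer that every efficacy endpoint needs a cut-off. Overall survival does not, because following patients through later therapy is normal there.
- A reader might infer that week-12 response is equally exposed. Section 18.2.2.4 already makes patients without a 12-week tumour assessment non-responders, and early discontinuers' scans usually miss week 12.
- A reader might take 8.5%, 14.2% and 22.5% as expected error rates. They arise only if every switcher is a certain success.

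**Conclusion.** The point holds for one definable patient: off pembrolizumab, not progressed, and on another systemic drug before the qualifying 12-week scan. For that patient the imaging rules conflict, and the primary outcome depends on which passage the site follows. Best objective response has the same open end. Week-12 response is largely protected, and overall survival is unaffected.

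The size cannot be fixed from the protocol. With one to three switchers, the false-positive probability at a true 15% goes from 4.8% to between 6.3% and 10.4% at an assumed 50% control rate, with upper bounds of 8.5% to 22.5%. There is no inflation if the control rate is 15% or less. The change is worth making because it is cheap and the decision threshold turns on single patients, not because a large bias has been shown.

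**What to change.** 1. Reconcile 10.4.2.3, 10.6, 10.6.1 and Appendix 1 note j into one rule on whether imaging continues after new anticancer therapy without progression.
2. In 18.2.1, state that a patient who starts non-protocol systemic anticancer therapy before the qualifying 12-week assessment counts as not progression-free.
3. In 18.2.2.4, state that scans taken after the start of such therapy do not contribute to best objective response.

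The cost is wording only. Additional anticancer treatment is already reviewed at the end-of-treatment and follow-up visits (10.5, 10.6, Appendix 1). The sample size of 48, the threshold of 12, the exact significance level of 4.8% and the power of 91.1% stay as they are for the stated 15% and 33%. The downside is that the primary rate and the best response rate may come out slightly lower.
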